### 2.5. Outcomes and Data Collection

Evaluations will be conducted at three time points: Baseline (T0), Intermediate at 8 weeks (T1), and Final at 32 weeks (T2).

Primary Outcome: The primary outcome will be pain intensity measured by the NRS [32,33].Secondary Outcomes: Psychosocial variables will include Kinesiophobia (Tampa Scale for Kinesiophobia, TSK-11) [50,51], Pain Catastrophizing (Pain Catastrophizing Scale, PCS) [52], chronic pain grade and related disability (Chronic Pain Grade Scale) [53], and health-related quality of life (SF-12) [54,55]. Physical performance will be evaluated using the Short Physical Performance Battery (SPPB) [56], the Timed Up and Go (TUG) test [57], handgrip strength (JAMAR Plus+ dynamometer; Performance Health, Warrenville, IL, USA) [58], and the force–velocity profile of the lower extremities (ADR linear encoder; ADR Inercial, Toledo, Spain) [59]. Changes in body composition (Tanita BC-418 Bioelectrical Impedance; Tanita Corporation, Tokyo, Japan) [60,61] and daily analgesic consumption will also be recorded. Additionally, adherence to the intervention will be rigorously monitored by recording participant attendance at all multicomponent exercise and Pain Neuroscience Education sessions. Finally, the Trail Making Test (TMT) will be administered at baseline to evaluate executive function and cognitive flexibility [62,63]. The inclusion of this instrument is based on an a priori secondary hypothesis that baseline levels of these capacities modulate the responsiveness to PNE, given that this educational intervention requires high cognitive flexibility to successfully reconceptualize the pain experience [22,26].

### 2.6. Sample Size and Statistical Analysis

The sample size was calculated based on the primary outcome (pain intensity via NRS). The estimation was performed using the GRANMO Version 8.0 tool. We calculated the effect size based on a Minimal Clinically Important Difference (MCID) of 1.5 points and a common standard deviation of 1.8. Assuming a two-sided contrast and an Analysis of Variance (ANOVA) for three independent groups, with an alpha level of 0.05, a statistical power of 80%, and an anticipated dropout rate of 10%, a minimum of 30 participants per group is required, resulting in a total sample of 90 subjects.

Intention-to-treat analysis will be performed. The primary endpoint for determining the long-term efficacy of the interventions is defined as the change in the primary outcome (NRS) at 32 weeks. Mixed-effects models for repeated measures will be used to evaluate intra- and intergroup changes over time (T0, T1, T2), considering the Group × Time interaction. To adjust for initial variance, baseline values of each respective outcome will be included as covariates in all models. Within this modeling framework, missing data will be inherently handled using restricted maximum likelihood (REML) estimation under the missing-at-random assumption. Additionally, to control for the inflation of Type I error associated with the analysis of multiple secondary outcomes, the Benjamini–Hochberg False Discovery Rate procedure will be applied. Furthermore, a secondary analysis stratified by sex will be conducted to evaluate potential differences in the intervention’s efficacy between men and women. Additionally, baseline TMT scores will be utilized as a covariate in an a priori secondary analysis to determine if baseline levels of executive function and cognitive flexibility modulate the treatment outcomes. The significance level will be set at *p* < 0.05.

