Based on this design, our primary hypothesis is that the combined intervention (PNE and exercise) will yield superior improvements in pain intensity, physical functionality, and psychosocial variables (such as kinesiophobia and catastrophizing) compared to exercise alone. Furthermore, we hypothesize that the extended 32-week PNE program will be significantly more effective in sustaining these clinical benefits and behavioral changes over time than the 8-week program. In addition to these clinical outcomes, we introduce an a priori secondary hypothesis regarding the moderating role of baseline cognitive flexibility and executive function, measured via the TMT. Chronic pain, particularly in older adults, often impairs these cognitive capacities [67,68,69]. Concurrently, PNE strictly requires pain reconceptualization, a process of unlearning deeply ingrained biomedical beliefs to adopt a biopsychosocial paradigm that inherently demands both of these cognitive functions [24,26]. Therefore, we propose that the baseline levels of executive function and cognitive flexibility will dictate the patient’s capacity to assimilate the educational intervention.

In the context of current literature, our protocol directly addresses several gaps identified in recent research. While recent meta-analyses and trials confirm that combining PNE with exercise yields significant clinical benefits in diverse populations, including older adults [28,36,37], most existing studies are limited by short intervention periods and a lack of long-term follow-ups. Furthermore, there is considerable heterogeneity regarding the optimal educational dosage. A recent dose–response meta-analysis established a threshold of 150 to 200 min of PNE to achieve clinically meaningful changes in pain and disability [42]. Our 8-week intensive phase (240 min) is specifically designed to safely exceed this threshold. However, considering the deep-rooted nature of maladaptive biomedical beliefs in older adults, short-term interventions might be insufficient to sustain behavioral changes. By introducing the 32-week maintenance arm, this trial expands upon current publications to explore whether sustained engagement and periodic reinforcement are required to consolidate pain reconceptualization and maintain active coping strategies over time.

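### The only between-arm term named for the analysis, the Group × Time interaction, does not test the 32-week primary endpoint, and the role of T0 in the model is left contradictory

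*Protocol article*

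**What the plan says.** Section 2.6 of the protocol article fixes the endpoint: "The primary endpoint for determining the long-term efficacy of the interventions is defined as the change in the primary outcome (NRS) at 32 weeks". The next sentence gives the analysis: "Mixed-effects models for repeated measures will be used to evaluate intra- and intergroup changes over time (T0, T1, T2), considering the Group × Time interaction". The sentence after that adds that "baseline values of each respective outcome will be included as covariates in all models".

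Section 2.6 names no contrast at week 32 and no pairwise arm comparison. The three-group ANOVA in the same section is only a sample-size assumption, built on a "Minimal Clinically Important Difference (MCID) of 1.5 points and a common standard deviation of 1.8".

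The Discussion states two hypotheses. The first is that PNE plus exercise beats exercise alone: "our primary hypothesis is that the combined intervention (PNE and exercise) will yield superior improvements in pain intensity, physical functionality, and psychosocial variables". The second concerns durability, that "the extended 32-week PNE program will be significantly more effective in sustaining these clinical benefits and behavioral changes over time than the 8-week program".

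**The concern.** An endpoint at one visit needs a between-arm comparison at that visit. A Group × Time interaction answers another question, and which one depends on how T0 enters the model.

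- **T0 as a response (T0, T1, T2).** The interaction has 4 df. Its null is that the arms have the same change at week 8 and the same change at week 32. A difference at either visit makes it false.
- **T0 as covariate, T1 and T2 as responses.** The interaction has 2 df. Its null is that the arm differences are the same at T1 and T2. A benefit gained by week 8 and fully kept satisfies that null, because it sits in the Group effect.

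The text supports both readings: one sentence lists T0 among the model's times, and a later one makes baseline a covariate in every model.

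The trial's question is whether benefit lasts. Table 1 shows that IG1 has no PNE after week 8 and that IG2 drops from two sessions a week to one every two weeks. A week-8 effect that fades is therefore a realistic result. A significant interaction could then be reported for the primary outcome with no difference at week 32.

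**Working it through.** **Inputs from section 2.6.** Difference 1.5 points, SD 1.8 (variance 3.24), alpha 0.05, 30 per arm, 10% dropout, hence 30 × 0.9 = 27 completers per arm.

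**Assumptions, not in the article.** Compound symmetry with correlation ρ = 0.3, 0.5 or 0.7 between visits; complete data on 27 per arm; the effect patterns below.

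**The plan's own figure.** A one-way ANOVA with range 1.5, SD 1.8 and 80% power needs 29 per arm (33 with dropout) if the middle mean lies midway, and 22 (25 with dropout) if two means coincide. The stated 30 arises when the middle mean is about 0.35 to 0.40 points from an extreme. The article does not give the middle mean, so 30 lies inside the open range of 25 to 33. It is not called wrong and does not bear on this point.

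**Tests compared** (noncentral F, noncentrality λ)

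- A: Group × Time with T0, T1 and T2 as responses, 4 and 154 df.
- B: Group × Time with T1 and T2 as responses and T0 as covariate, 2 and 78 df.
- C: between-arm test at T2 adjusted for T0, 2 and 78 df.

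With control at 0 and both PNE arms at −1.5, the squared deviations of the three arm means sum to 1.5² × 2/3 = 1.5.

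**Pattern 1: both PNE arms 1.5 points better at week 8, no difference at week 32.**

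- A: the changes T1−T0 and T2−T0 have covariance 3.24(1−ρ) × [[2, 1], [1, 2]]. Inverting gives λ = 27 × 1.5 × (2/3) / [3.24(1−ρ)] = 27 / [3.24(1−ρ)].
- B: T2−T1 has variance 2 × 3.24(1−ρ) and is uncorrelated with T0, so λ = 27 × 1.5 / [6.48(1−ρ)].
- C: λ = 0.

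| ρ | A: λ, rejects | B: λ, rejects | C rejects |
|---|---|---|---|
| 0.3 | 11.90, 78.5% | 8.93, 75.0% | 5% |
| 0.5 | 16.67, 91.5% | 12.50, 88.4% | 5% |
| 0.7 | 27.78, 99.4% | 20.83, 98.5% | 5% |

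**Pattern 2: both PNE arms 1.5 points better at week 8 and week 32.**

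- A: the same λ as in pattern 1, because the quadratic form takes the same value.
- B: the T2−T1 difference is zero in every arm, so λ = 0.
- C: the variance given T0 is 3.24(1−ρ²), so λ = 27 × 1.5 / [3.24(1−ρ²)].

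| ρ | A rejects | B rejects | C: λ, rejects |
|---|---|---|---|
| 0.3 | 78.5% | 5% | 13.74, 91.3% |
| 0.5 | 91.5% | 5% | 16.67, 95.7% |
| 0.7 | 99.4% | 5% | 24.51, 99.5% |

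**Pattern 3: IG1 fades to no difference at week 32, IG2 holds 1.5 points.** A rejects in 93.4%, 98.7% and nearly 100%; B in 75.0%, 88.4% and 98.5%; C in 91.3%, 95.7% and 99.5%.

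**Simulation check.** For A, 4,000 runs of the random-intercept F-test gave 79.3%, 91.5% and 99.4% in pattern 1, 78.8%, 91.7% and 99.3% in pattern 2, and 4.5–5.4% under no effect. A multivariate version of A (Wilks' lambda on the two change scores, 2,000 runs) gave 77.4%, 89.2% and 98.8% in pattern 2.

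**Both roles for T0 at once.** With complete data and a random intercept, adding baseline as a main-effect covariate while T0 stays in the response does not change test A. Doing both therefore does not repair the mismatch.

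**The case against.** The strongest reply is that the article never says the interaction p-value decides anything. It says only that the interaction will be considered, directly after fixing the endpoint at 32 weeks. Read together, the two sentences can mean: fit the repeated-measures model and judge efficacy at week 32. The interaction term is what allows a visit-specific contrast, and the fix below keeps it. Choosing the contrast could also be left to an analysis plan that is not shown. This stands in part. A reader might infer that the trial has prespecified a wrong primary test; the text does not support that.

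A reader might also infer that the interaction over T0, T1 and T2 misses a sustained benefit. It does not. With T0 as a response, a sustained difference is itself an interaction and is detected, with some loss of power. The miss belongs only to the model with T1 and T2 as responses. Even there the benefit appears in the Group effect of the same model, and nothing bars reporting it.

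Finally, if IG1 fades and IG2 holds, as the second hypothesis suggests, the interaction has good power under either coding (pattern 3). That is true, but a rejection still would not show at which visit the arms differ.

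What remains is more than an omitted detail. The text names one between-arm term, that term has a different null from the endpoint, and the sentences around it disagree on whether T0 is a response or a covariate.

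**Conclusion.** The point holds in a limited, conditional form. If the Group × Time interaction is used to judge the primary outcome, a 1.5-point effect present only at week 8 rejects it in about 75–99% of trials under either coding of T0, against 5% for the 32-week test.

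A fully sustained 1.5-point effect is missed (about 5% rejection) only under the covariate coding, which the baseline sentence supports. With T0 as a response it is detected in roughly 77–99%, against 91% to over 99% for the baseline-adjusted 32-week test.

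The percentages depend on the assumed correlation, compound symmetry, 27 completers per arm and the chosen effect patterns. The difference between the nulls does not depend on them.

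**What to change.** In section 2.6, or in the analysis plan with a matching line in the protocol, state that:

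- T1 and T2 are the responses and T0 is the covariate. T0 cannot sensibly be both, since at T0 the response would equal its own covariate.
- The primary test is the baseline-adjusted between-arm contrast in NRS at T2, estimated from that model. Say which arms are compared.
- The Group × Time terms stay in the model, but their F-test neither decides nor gates the primary conclusion.
- The T1 contrasts are secondary.

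This needs a few sentences, no new data and no more participants. At 27 per arm the three-arm T2 test keeps 5% error under a week-8-only effect and has over 90% power for the sustained 1.5-point effect, under the assumptions above. The downside is that an effect seen only at week 8 can no longer support a primary claim.

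### Baseline pain is both a repeated response (T0) and a covariate in the same mixed model, so the promised baseline adjustment drops out of the 32-week change contrast

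*Protocol article*

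**What the plan says.** Section 2.5 of the protocol article sets three assessments and identifies T0 as baseline, T1 as week 8 and T2 as week 32. Section 2.6 then gives the analysis: "Mixed-effects models for repeated measures will be used to evaluate intra- and intergroup changes over time (T0, T1, T2), considering the Group × Time interaction". It goes on to say that "baseline values of each respective outcome will be included as covariates in all models", with the stated aim of accounting for initial variability. The primary endpoint is "defined as the change in the primary outcome (NRS) at 32 weeks". Estimation is by REML, assuming data missing at random.

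The article does not say that T0 leaves the response once it becomes a covariate, that the response is a change score at T1 and T2, or that baseline means are held equal across arms. It names no covariance structure.

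**The concern.** Two instructions in the same paragraph conflict. T0 is named as a level of Time, and within-group change from baseline needs T0 in the model. If T0 is a response and the baseline value is also a covariate, response and covariate are identical on every T0 row. A model built that way does not deliver the adjustment that the plan promises.

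The instruction governs the primary endpoint and every secondary outcome. What is at stake is mainly precision in a trial of 90 people. In addition, the same fitted model can yield two group comparisons with different error rates, so the choice of output matters.

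**Working it through.** **Inputs.** From section 2.6: difference 1.5 points, SD 1.8, two-sided alpha 0.05, 30 per group, 10% dropout, hence 30 × 0.9 = 27 evaluable per arm. Assumed, because the article does not give them: correlation r between visits (0.3 to 0.8), the covariance structure, and that 1.8 is the SD of a single NRS score.

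**The plan's own figure.** The pattern of the three means is not stated. A three-group ANOVA with a range of 1.5 needs 22 per group (25 with dropout) if one mean differs, and 29 (33 with dropout) if the means are equally spaced. The stated 30 lies between these. Nothing below depends on it beyond the 27 evaluable.

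**1. Group × Time contrast, T0 to T2.** The covariate adds the same amount, slope × baseline, to a person's T0 and T2 rows, so it vanishes from T2 − T0. In simulated complete data (30 per arm, SD 1.8, random intercept, REML, 4,000 null trials per correlation), the estimates with and without the covariate differed by at most 8 × 10⁻¹⁵. Type I error at r = 0.3, 0.5 and 0.7 was 5.7%, 5.5% and 4.9% with the covariate, and 5.5%, 5.5% and 4.9% without it. What remains is a raw change-score comparison.

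**2. Cost in precision.** Per-person variance is 2(1 − r)SD² for change and (1 − r²)SD² after proper baseline adjustment. The ratio is 2(1 − r)/(1 − r²) = 2/(1 + r). The SE of a two-arm difference is √(2 × variance/27), and power is Φ(1.5/SE − 1.96), pairwise and without multiplicity correction.

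| r | Variance ratio | SE, change | SE, adjusted | Power, change | Power, adjusted |
|---|---|---|---|---|---|
| 0.3 | 1.54 | √(2 × 4.536/27) = 0.580 | √(2 × 2.948/27) = 0.467 | 73% | 89% |
| 0.5 | 1.33 | √(2 × 3.240/27) = 0.490 | √(2 × 2.430/27) = 0.424 | 86% | 94% |
| 0.7 | 1.18 | √(2 × 1.944/27) = 0.379 | √(2 × 1.652/27) = 0.350 | 98% | 99% |

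**3. If the baseline-adjusted group difference at T2 is read instead (random intercept assumed).** The single slope averages 1 at T0 and r at T1 and T2: (1 + 2r)/3, or 0.667 at r = 0.5. In units of SD², the residual variance is then (1 − 0.667)² = 0.111 at T0 and 1 − 2 × 0.667 × 0.5 + 0.667² = 0.778 at T1 and T2. The model pools these to (0.111 + 2 × 0.778)/3 = 0.556 and applies that at T2. Reported SE over true SE is √(0.556/0.778) = 0.845, so type I error is 2Φ(−1.96 × 0.845) = 9.8%. In general the variance ratio is (4 + 2r)/(5 + 4r). SE ratios are 0.861, 0.845, 0.832 and 0.826 at r = 0.3, 0.5, 0.7 and 0.8, giving 9.1%, 9.8%, 10.3% and 10.5%. In the simulation, type I error was 9.3%, 10.5% and 10.2% at r = 0.3, 0.5 and 0.7. With T0 removed from the response it was 5.8%, 5.5% and 5.0%.

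**4. If the covariance is unstructured.** As the baseline slope approaches 1, the T0 residual variance goes to 0 and the likelihood rises without limit. In one simulated data set of 90 people the REML log-likelihood was −125 at slope 0, 271 at 0.99 and 865 at 0.99999. There is no finite maximum.

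**The case against.** The strongest reply is that the article never literally calls T0 a response. The bracketed time points may only describe the period over which change is studied. If NRS, or its change, at T1 and T2 is the response, baseline as covariate is standard and sound. A journal article may also leave the response vector and covariance structure to an analysis plan. This stands in part: the authors may have intended that model. But the published sentence puts T0 beside Group × Time and within-group change, so the conflict is in the text and not a missing detail. The sentence would still need correcting.

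A reader might infer that the primary test has a false-positive rate of about 10%. The documents do not support that. The figure belongs to the adjusted difference at T2 under a random intercept, whereas section 2.6 names change at 32 weeks and Group × Time, for which the error rate is near 5% under equal correlations. With unequal correlations (0.6 between adjacent visits, 0.4 between T0 and T2), a random-intercept model gave 8.7% for that contrast both with and without the covariate. That excess comes from the assumed covariance, not from the double use of baseline.

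It is also fair to say that the sample size claimed no gain from a covariate, and that at r = 0.5 the change contrast still has 86% power, above the planned 80%. If 1.8 is meant as the SD of change, power is 86% at any r. The efficiency loss remains, but falling below 80% depends on a low correlation.

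**Conclusion.** The point holds as an error in the written model. Taken at its word, section 2.6 uses baseline twice, and for the contrast that best matches the stated endpoint the promised adjustment does not occur. That test remains valid under equal correlations but is inefficient, with 18% to 54% more variance than a proper baseline-adjusted analysis for r from 0.7 down to 0.3. Pairwise power at the planned difference falls from 89% to 73% at r = 0.3 and from 94% to 86% at r = 0.5, if 1.8 is the SD of a single score.

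Exact cancellation needs complete data. With 10% missing at T2 and r = 0.5, individual estimates with and without the covariate differed by up to 0.21 points, and type I error was 6.4% against 6.1%.

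The other two faults are conditional and cannot occur together. An SE that is 14% to 17% too small, with type I error of about 9% to 10%, requires a random-intercept model and reading the adjusted T2 difference. A degenerate fit requires an unstructured covariance, and would probably show as a failed or singular fit rather than a silently wrong result.

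**What to change.** Choose one of two models and state it in section 2.6.

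- Use only T1 and T2 as responses, with arm, time, arm × time, baseline, baseline × time and an unstructured covariance. Read the primary result as the arm contrast at T2.
- Or keep T0 as a response, with one baseline mean common to the three randomised arms and no baseline covariate.

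Do not do both. Under either option, name the T2 contrast and the covariance structure before analysis. The structure matters in its own right: with the unequal correlations above, the first option fitted with only a random intercept still gave 7.3% type I error. If T1 and T2 were always meant to be the only responses, correct the sentence that lists T0 in the model. The cost is one sentence and no new data.

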## 2. Materials and Methods

### 2.1. Study Design

This study has been designed as a prospective, longitudinal, randomized controlled trial with three parallel groups and a 1:1:1 allocation. The protocol follows the guidelines of the CONSORT (Consolidated Standards of Reporting Trials) statement for non-pharmacological clinical trials [43]. The study will have a total duration of 12 months, with a 32-week intervention period. The flow of participants through each stage of the trial is depicted in Figure 1.

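### Section 2.6 would judge whether efficacy differs by sex from separate analyses in men and women at p < 0.05, which would often suggest a difference that does not exist

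*Protocol article*

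**What the plan says.** Section 2.6 of the protocol article makes change in NRS at 32 weeks the primary endpoint and analyses it with a mixed model for repeated measures in which the Group × Time interaction is the named term. It applies Benjamini–Hochberg "to control for the inflation of Type I error associated with the analysis of multiple secondary outcomes". It then adds that "a secondary analysis stratified by sex will be conducted to evaluate potential differences" in efficacy between men and women, and closes with a single significance level of p < 0.05, to which no exception is made.

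The sex analysis is called secondary, not exploratory. No group-by-sex term is mentioned. The outcomes and contrasts to be examined within each sex are not listed.

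**The concern.** The stated aim is comparative: does the intervention work differently in men and women? The stated method is stratification, which yields one set of p-values in men and another in women. Two problems follow.

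- **No true effect.** Running the NRS analysis twice gives two chances of a nominally significant result. NRS is the primary outcome, so these results lie outside the false discovery rate step as worded.
- **Equal true effect in both sexes.** Each sex holds only part of a trial of 90 people in three arms, so power within a sex is low. One sex will often reach p < 0.05 while the other does not. That pattern is easily read as a sex difference, although it reflects only sampling variation and stratum size.

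At stake is a published statement that adding pain neuroscience education helps one sex and not the other, which the data would not support.

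**Working it through.** **Inputs from the document.** Effect and spread (Section 2.6): "Minimal Clinically Important Difference (MCID) of 1.5 points and a common standard deviation of 1.8". From the same section, in summary: two-sided testing by ANOVA over the three arms, alpha 0.05, power 80%, dropout 10%, giving 30 per group and 90 in total. The arms are equally allocated (Section 2.1). Completers per arm: 30 × 0.9 = 27. The sex mix is not stated, so 50:50, 70:30 and 80:20 are assumed.

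**The plan's own figure.** A one-way ANOVA on these inputs needs 29 per group if the three means are equally spaced (29 / 0.9 = 32.2, so 33), or 22 if one mean is shifted by 1.5 (22 / 0.9 = 24.4, so 25). The stated 30 lies between 25 and 33. The pattern of means is not given, so 30 cannot be reproduced uniquely. Nothing below depends on it beyond the 27 completers.

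**1. No true effect, NRS only, alpha 0.05 in each sex.** Men and women are separate people, so the two strata are independent and the chance of at least one significant result is 1 − (1 − p)², where p is the rate within one sex.

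| Tests within each sex | p within a sex | Either sex |
|---|---|---|
| One omnibus test | 0.05 | 1 − 0.95² = 9.75% |
| Two contrasts against control | about 0.09 | about 17% |
| Three unadjusted pairwise contrasts | 0.1223 | 1 − 0.8777² = 23.0% |

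The 0.1223 is the probability that the range of three independent standard normal values exceeds 1.96 × √2. Simulation with t tests and 5 to 22 people per arm per sex gives 22% to 23% for the last row, so the sex split hardly matters here. If pairwise contrasts are examined only after a significant omnibus test, the figure returns to about 9.7%.

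These rates count both directions. Counting only results that favour education, or the longer programme, gives about 8.8% (two contrasts) or 12.5% (three contrasts).

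**2. Equal true effect of 1.5 points in both sexes, SD 1.8.** For one pairwise contrast by a two-sample t test with n per arm in that sex, the noncentrality is 1.5 / (1.8 × √(2/n)) on 2n − 2 degrees of freedom. With powers P and Q in the two sexes, the chance of significance in exactly one is P(1 − Q) + Q(1 − P).

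| Sex mix | n per arm | Noncentrality | Power | Significant in exactly one sex |
|---|---|---|---|---|
| 50:50 | 13.5 / 13.5 | 2.17 / 2.17 | 0.548 / 0.548 | 50% |
| 70:30 | 18.9 / 8.1 | 2.56 / 1.68 | 0.703 / 0.346 | 56% |
| 80:20 | 21.6 / 5.4 | 2.74 / 1.37 | 0.762 / 0.231 | 64% |

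For example, at 50:50: 2 × 0.548 × 0.452 = 0.495.

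**3. The direct comparison.** One group-by-sex test on NRS has a 5% false-positive rate, whatever the main effect. For one contrast at 50:50, the standard error of the difference between the sexes is 1.8 × √(2/13.5 + 2/13.5) = 0.98, so the 95% interval is about ±1.9 points. At 80:20 it is 1.8 × √(2/21.6 + 2/5.4) = 1.22, or about ±2.4 points.

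**The case against.** Several points on the other side stand.

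- **The 23% is not the plan's named test.** A reader might infer a 23% chance of a false efficacy claim in one sex. That needs three unadjusted pairwise contrasts in each sex, which Section 2.6 does not list. The term it names, tested once per sex, gives 9.75%. The 23% also includes results against education. Pairwise contrasts are not far-fetched, because the Discussion hypothesises both combined treatment over exercise and 32 over 8 weeks of education. Still, 23% is the upper end of a range.
- **There is a hierarchy.** NRS at 32 weeks is the primary endpoint and the sex analysis is called secondary. The aim is worded as a comparison, and the stated hypotheses do not mention sex. The article leaves room for a claim within one sex but does not announce one.
- **The 50% to 64% is a matter of power, not multiplicity.** That is right, and a multiplicity adjustment would not cure it. It is why the fix is a direct comparison. The calculation also uses a plain t test, while the planned model adjusts for baseline and may be more precise. Even with 80% power in each sex, though, exactly one would be significant in 2 × 0.8 × 0.2 = 32% of trials.
- **Detail may sit in an analysis plan that is not shown.** That covers the list of contrasts. It does not fully cover the article's own pairing of a comparative aim with a stratified method and a general p < 0.05.

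A reader might also extend the point to the Trail Making Test, since "baseline TMT scores will be utilized as a covariate in an a priori secondary analysis to determine if baseline levels" modulate outcomes, and the Discussion says "we propose that the baseline levels of executive function and cognitive flexibility will dictate" how well patients take in the education. The documents do not support that extension. This is one moderation hypothesis set in advance, and testing one such hypothesis at 5% is not in itself inflation. The choice of score and error family can be left to the analysis plan.

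**Conclusion.** The point holds for the sex analysis only, as a cheap improvement rather than a flaw in the primary analysis. The method named in Section 2.6 does not answer the question it sets. With no effect, a nominally significant NRS result in at least one sex has a chance of about 10% to 23%, in either direction, depending on contrasts the article does not state. With an equal effect of 1.5 points, one contrast would be significant in exactly one sex in about half of trials or more (50% to 64%). That range assumes SD 1.8, 27 completers per arm, a simple t test and a sex mix between 50:50 and 80:20. A more precise model would change these percentages.

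**What to change.** In Section 2.6, replace the sentence on stratification by sex with wording to this effect:

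- The difference in efficacy between men and women is assessed by a group-by-sex (by time) term in the mixed model for NRS at week 32.
- Sex-specific effects are reported as estimates with 95% confidence intervals.
- The analysis is exploratory, and no efficacy claim is made for one sex from a within-sex p-value.

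This costs two or three sentences and changes nothing in design, sample size or data collection. There are two downsides. A nominal p < 0.05 in one sex can no longer be reported as a finding. The interaction test also has low power: with a standard error of 0.98 at 50:50, a true difference between the sexes as large as 1.5 points would be detected only about a third of the time (1.5 / 0.98 = 1.53, below the critical 1.96). The intervals will show that imprecision openly.

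### The TMT moderation hypothesis is tested with a covariate term that contains no moderation parameter, and the sex-stratified analysis states no comparison of the sexes

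*Protocol article*

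**What the plan says.** The hypothesis appears twice in the protocol article. Section 2.5 justifies collecting the TMT by an "a priori secondary hypothesis that baseline levels of these capacities modulate the responsiveness to PNE". Section 5 (Discussion) repeats it as an "a priori secondary hypothesis regarding the moderating role of baseline cognitive flexibility and executive function". Both describe effect modification: the benefit of PNE over exercise alone should vary with baseline cognition.

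Section 2.6 gives the method: "baseline TMT scores will be utilized as a covariate in an a priori secondary analysis to determine if baseline levels of executive function" (the sentence then adds cognitive flexibility and states the aim as modulation of outcome). In the same paragraph, the word covariate is also used for plain adjustment: "baseline values of each respective outcome will be included as covariates in all models". The one interaction named is in the main model, "considering the Group × Time interaction". No term combining group with TMT or with sex is named.

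On sex, section 2.6 says that "a secondary analysis stratified by sex will be conducted to evaluate potential differences in the" efficacy of the interventions for men and women. It does not say how the two strata will be set against each other.

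**The concern.** The TMT model as described does not contain the quantity that the hypothesis is about. A common TMT slope applies equally to the control arm, which receives no PNE (Table 1). A significant coefficient would show that cognition is related to pain, and it could easily be reported as evidence that cognition governs response to education. A null coefficient could hide true moderation. The TMT is administered specifically for this hypothesis, and the hypothesis is billed as a priori. If the interaction is added only after the data are seen, that status is lost.

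The sex analysis raises a milder form of the same problem. Its stated aim is a difference between two effects, but the text stops at estimating each effect separately.

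**Working it through.** The plan gives no figure for either analysis, so there is none to reproduce. The inputs from section 2.6 are a "Minimal Clinically Important Difference (MCID) of 1.5 points and a common standard deviation of 1.8", 30 participants per group and 10% dropout, hence 30 × 0.9 = 27 completers per arm. The TMT slopes and the share of men are assumptions.

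**TMT: what the stated term estimates.** Take week 32, with G1 and G2 indicating the two PNE arms and T the TMT score in SD units.

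- Covariate only: E(Y) = α + β1·G1 + β2·G2 + γ·T. The effect of IG1 versus control at T = t is (α + β1 + γt) − (α + γt) = β1, whatever t is. The model fixes the PNE effect as constant across TMT, which is the null of the moderation hypothesis.
- With interaction: add δ1·G1·T + δ2·G2·T. The effect becomes β1 + δ1·t. Moderation means that δ1 or δ2 differs from zero.

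With equal arms, the single slope γ is roughly the mean of the three arm-specific slopes, so it responds to that mean and not to differences between arms.

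**TMT: simulation.** 4,000 runs per scenario, one time point, 27 per arm, residual SD 1.8, PNE effect 1.5 points in both PNE arms, two-sided 5% tests. The interaction test has 2 df.

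| Control slope (points per SD) | Extra slope in PNE arms | Covariate significant | Interaction significant |
|---|---|---|---|
| 0.6 | 0 | about 82% | about 5% |
| −0.5 | 0.75 | 5–6% | about 30% |
| 0 | 0.75 | about 63% | about 29% |
| 0 | 1.0 | about 86% | about 49% |

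In row 1 there is no moderation, yet the covariate is usually significant. In row 2 there is moderation, but the mean slope is (−0.5 + 0.25 + 0.25)/3 = 0 and the covariate does not see it. In rows 3 and 4 the covariate is often significant, but only because the mean slope is non-zero. That result looks no different from row 1.

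**Sex: an illustration.** Suppose the strata were compared by their separate p-values, and the true effect were 1.5 points in both sexes. For one PNE-versus-control contrast with a two-sample t-test, d = 1.5/1.8 = 0.83. If pM and pW are the power in men and women, P(exactly one significant) = pM(1 − pW) + pW(1 − pM).

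| Assumed share of men | Men / women per arm | pM | pW | Exactly one significant |
|---|---|---|---|---|
| 20% | 5 / 22 | 0.21 | 0.77 | about 65% |
| 30% | 8 / 19 | 0.34 | 0.71 | about 56% |
| 40% | 11 / 16 | 0.46 | 0.63 | about 51% |

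**Precision of the corrected sex analysis.** The SE of the difference between the sex-specific effects is 1.8·√(2/nM + 2/nW). With 8 men and 19 women per arm this is 1.8·√(0.250 + 0.105) = 1.07, so the 95% CI is about ±1.96 × 1.07 = ±2.1 points. By normal approximation, power to detect a 1.5-point sex difference is about 23% to 33% for 80% down to 50% women.

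**The case against.** The strongest reply on TMT is that covariate is shorthand in a condensed article. The same sentence and two other sections make the intended question clear, and an analysis plan that is not shown may contain the interaction. That is possible, and the article does not rule an interaction out. But the point is not about missing detail. The article states a method, and the method as stated answers a different question. The same paragraph names an interaction where one is meant and uses covariate for baseline adjustment. If an interaction was intended, the wording still needs correcting.

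On sex, the objection largely stands. A reader might infer that a stratified analysis cannot show a sex difference at all. That goes too far: the two stratum estimates are independent, and testing their difference is equivalent to an interaction test. A reader might also take the 51–65% as the false-positive rate of the plan. It is not. It would be an error rate only if a sex difference were declared whenever one stratum was significant and the other was not, and the article states no such rule. The figure also covers one pairwise contrast and ignores baseline adjustment. At an assumed baseline correlation of 0.5, the 30%-men case stays near 54%.

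Finally, the corrected tests have low power at N = 90, so the TMT hypothesis may remain unsettled after the change. That is true, and it limits how much the correction can deliver. It does not justify a model that tests something else.

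**Conclusion.** The TMT point holds. Read as written, section 2.6 cannot test the moderation hypothesis of sections 2.5 and 5, because the stated model has no parameter for it. This follows from the form of the model and needs no assumption. The simulated rates (about 82% significant under pure prognosis, 5–6% under moderation with zero mean slope) depend on assumed slopes and show only that the error can run in either direction.

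The sex point holds in a narrower form: the aim is a difference between men and women, and no comparison of the strata is stated. The 51–65% range illustrates the risk of comparing p-values, under an assumed 20–40% men and equal true effects. It does not describe what the plan says it will do.

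A reader might conclude that the main result of the trial is compromised. The documents do not support that: both analyses are labelled secondary, and the week-32 pain comparison does not use them. The point should be fixed, at a severity below that of a flaw in the primary analysis.

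**What to change.** **TMT.** Choose one continuous TMT score in advance. In the whole-sample model, include its main effect and TMT × group (× time). Base any moderation claim on the week-32 TMT × (PNE versus control) contrast with its 95% CI, and say in advance whether the two PNE arms are taken together or separately. Do not interpret the TMT main effect as moderation.

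**Sex.** Add sex and sex × group (× time) to the whole-sample model, or test the difference between the two stratum estimates. Report that difference with its CI, next to the by-sex effects.

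Label both analyses exploratory on grounds of precision.

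**Cost.** A wording change and a few model terms, made before the data are seen. No extra participants or measurements are needed. The drawback is wide intervals, about ±2.1 points for the sex difference in the 30%-men case, which reflect the information that 90 participants can give.
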